### Trial allocation, sequence generation, and blinding

Allocation to treatment arms will be randomly assigned in a 2:1 ratio using permutated block randomisation. Unblinded researchers independent to the study team, utilising a simple randomisation method, will develop the randomisation sequence and assign participants to study arms. The unblinded researchers will allocate and package enema kits sequentially, and packaging will be identical to conceal treatment allocation and blinding. The study staff, investigators, trial biostatistician, nurses delivering the enemas, and participants will be blinded to group allocations.

### Data storage and management

Participants will be allocated a unique study ID number on enrolment, and their data will be de-identified and coded with this unique study ID. Blood and stool samples collected will be stored in a minus 80 °C until analysis. Faecal samples will be sent to the Queensland-based laboratory, Microba, for metagenomic analysis. DNA will be extracted and then sequenced using an Illumina NovaSeq high-throughput sequencing platform. The sequences allow the microorganisms in the samples to be classified by comparing against reference databases so that the presence and abundance of the microorganisms present can be identified and reported. Questionnaire and other study data will be collected online and stored using the secure Deakin University REDCap server.

All written and electronic data, including source documents, informed consent forms, and ethics approval forms will be retained for at least 15 years from the end of the study, as is the GCP requirement for clinical trials. All research data from consenting participants, including gut microbiota sequencing data and pre-processing and analysis pipeline information, will also be stored in a secure data repository (Deakin Research Online) for long-term preservation and/or reuse by other researchers with appropriate ethical approval/consideration from their institution (for example, meta-analyses).

### Data analysis and reporting

Reporting of findings will be in accordance with CONSORT extension for pilot and feasibility trials [59]. The study biostatistician responsible for the analysis of outcome data, as well as participants and patient assessors, will be blind to group allocation.

### Impact of and response to participant withdrawal

Participants will be withdrawn from the study if they withdraw consent or at the discretion of the researcher given adverse events or loss to follow-up. Reasons for withdrawal will be documented, and participants will be asked whether they are willing to accept any further contact to assess short- and longer-term safety.

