### Procedure

Participants will receive either four active or four placebo FMT delivered via an enema will be administered over four consecutive days to each participant by a research nurse. Assessments will be conducted at baseline, and then every 2-weeks until the primary end point (8 weeks). A further follow-up assessment will then occur at week 26 to capture long-term safety data. An outline of the study schedule is provided in Table 1 and the appointment schedule is summarised in Fig. 1. Participants, investigators, assessors, and study statisticians will be blinded to group allocation. This protocol is reported as per the Standard Protocol Items: Recommended for Intervention Trials (SPIRIT) guidelines [58], and the CONSORT extension for pilot and feasibility trials checklist [59]. All study procedures will be concordant with Good Clinical Practice (GCP) principles. The consent procedure is described below under the heading Consent and Enrolment.

**Table 1 Tab1:** Schedule of assessments, instruments, and procedures to be implemented at each study appointment

Variable	Instrument	*Week (first row)* Appointment number (second row)										
		*− 2*		*0 (baseline)*				*2*	*4*	*6*	*8*	*26*
		1a	1b	2	3	4	5	6	7	8	9	10
Screening (via Telehealth)												
Enrolment	Informed consent	✓										
General inclusion criteria	Eligibility screener for entrance criteria	✓										
Alcohol and substance abuse	Alcohol Use Disorders Identification Test (AUDIT) Drug Abuse Screening Test (DAST-10)	✓										
Diagnosis of MDD	Structured Clinical Interview for the DSMI-V (SCID-V) mood disorders module		✓									
Depression severity and suicidality	Montgomery-Asberg Depression Rating Scale (MADRS)		✓									
Study appointments												
Group allocation	Randomisation spreadsheet			✓								
FMT	Enema-delivery of intervention or placebo			✓	✓	✓	✓					
Demographics	General questionnaire			✓								
Medical history	Medical history Standard psychiatric assessment Family history		✓ (optional)	✓								
Study appointments continued.												
Medication use	Current medications Medication history		✓	✓								
Personality disorders	Personality disorders (SAPAS)			✓								
Diet	Diet (Simple Dietary Questionnaire)			✓							✓	
Psychological symptoms	Depression, Anxiety and Stress symptomatology (DASS) Depression severity (MADRS) Suicidality (MADRS)			✓				✓	✓	✓	✓	
Gut symptoms	Gastrointestinal Symptom Rating Scale (GSRS)			✓				✓	✓	✓	✓	

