Medical variables	Change in medications, vaccines, illness, etc			✓				✓	✓	✓	✓	
General health and functioning	Patient Global Impression of Change Sheehan Disability Scale Sleep (Pittsburgh Sleep Quality Index) Quality of Life			✓				✓	✓	✓	✓	
Study appointments continued.												
Changes of circumstance	Medication changes questionnaire			✓				✓	✓	✓	✓	
Cost analysis	Resource Utilisation Questionnaire			✓							✓	
Physical examination	Height (stadiometer) Weight (scales) Blood pressure (sphygmomanometer) Heart rate (sphygmomanometer)			✓				✓			✓	
Blood samples	Whole blood by research nurse/ACL			✓				✓			✓	
Stool samples	Microba stool collection kits			✓				✓			✓	
Feasibility data												
Tolerability	Adverse events			✓	✓	✓	✓	✓	✓	✓	✓	✓
Adequacy of blinding	Participant questionnaire							✓				
Adherence	Monitoring questionnaire completion and appointment attendance throughout the study period			✓	✓	✓	✓	✓	✓	✓	✓	
Acceptability	Study Participant Feedback Questionnaire Specific questions pertaining to study intervention			✓				✓			✓	
Researcher/trial feasibility data												
Recruitment	Monitoring of recruitment rates by study staff throughout trial period			✓	✓	✓	✓	✓	✓	✓	✓	
Retention	Monitoring of trial attrition by study staff throughout trial period			✓	✓	✓	✓	✓	✓	✓	✓	

The study schedule allows for flexibility for all or parts of each appointment to be conducted by telehealth if this is preferable to the participant or required for other reasons

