### Study setting

The trial will be conducted at a dedicated clinical trials facility at University Hospital Geelong, Victoria. This space includes appropriate consultation spaces and on-site equipment for intervention delivery and the collection of biological samples. This study will consist of 10 study appointments, six of which are in-person and four via telehealth (see Table 1 and Fig. 1).

The collection of blood samples will be performed by a qualified research nurse or phlebotomist, where markers of cardiovascular and metabolic disease risk (e.g. lipids, HbA1c, and blood glucose) will be assayed. Additional blood samples will be collected and transported to the Geelong Centre for Emerging and Infectious Disease (GCEID) laboratories in Geelong for additional blood analyses and long-term storage.

Stool samples will be collected by participants at home using a Microba (Queensland, Australia) stool sampling kit. Participants will then return the completed kits to research personnel at their study appointments. These stool samples will be de-identified (marked with a participant code only) and sent to Microba for metagenomic analyses.

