
### Feasibility targets

Table 4 outlines pre-specified targets identified by the research team as a minimum standard that would indicate that the study design was feasible. These targets will also assist the study team to identify aspects of the trial that may need to be amended to improve future, large-scale trials.

**Table 4 Tab4:** Feasibility targets

Target area	Feasibility target
Recruitment	Successful enrolment of *n* = 15 participants across a 6-month active recruitment period
Retention	A minimum of *n* = 10 participants to complete study until the 8-week primary endpoint (i.e. a 33% attrition rate).
Adherence to protocol	Participants should: 1) Receive two of the total four enemas 2) Attend their baseline, week 2 and week 8 appointments 3) Provide baseline and week 2 stool samples
Safety	Nil severe and/or serious adverse events rated as likely due to study intervention in the active FMT group.
Adequacy of blinding	The best achievable outcome for adequacy blinding is participants and researchers correctly guessing allocation at a rate of 50% (the rate due to chance). Whilst we are not likely to be statistically powered to measure this outcome, we aim to reach an outcome approaching 50%.

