#### Safety requirements

Study participants will be provided with contact details for the research team, and strongly encouraged to contact the research team at any point in the study to report adverse events or discuss concerns. In addition to this, there will be routine contact made every 2 weeks post-intervention until the 8-week primary endpoint, and an additional 26-week follow-up, to assess adverse events or side effects. In the circumstance of a severe or serious adverse event, participants will be encouraged to attend medical services.

If a severe or serious adverse event occurs, the re-identification protocol may need to occur, so that treating clinicians can know whether the participant received the FMT intervention or the placebo. Each participant will be issued a unique identifying number on enrolment which will be linked to the intervention that they were allocated. The unblinded research assistant will be contacted to reveal the treatment allocation of the participant, only if necessary for their medical care.

A data safety monitoring board (DSMB) will be implemented comprising of a clinician, a statistician, and a pharmacist. All members of the DSMB will be independent of the research to avoid conflicts of interest. The role of the DSMB will be to oversee the safety of the study. This will involve reviewing the study protocol, PICF and consent procedures, safety monitoring procedures, procedures relating to confidentiality and adverse events arising during the course of the study. In the event of a severe or serious adverse event, the DSMB will be promptly notified and will decide on whether to pause recruitment or halt the study.

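### The withdrawal rule lets the researcher remove a still-consenting participant from the whole study after an adverse event, so that later safety follow-up needs fresh agreement

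*Protocol article*

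**What the plan says.** The section Impact of and response to participant withdrawal states that participants will be "withdrawn from the study if they withdraw consent or at the discretion of the researcher given adverse events", or on loss to follow-up. Reasons are documented, and "participants will be asked whether they are willing to accept any further contact to assess short- and longer-term safety".

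Under Procedure, the four enemas "will be administered over four consecutive days to each participant by a research nurse". The same section adds: "A further follow-up assessment will then occur at week 26 to capture long-term safety data". Safety requirements says that "there will be routine contact made every 2 weeks post-intervention until the 8-week primary endpoint, and an additional 26-week follow-up" to look for adverse events. It does not say whether this contact continues for a participant whom the researcher has withdrawn.

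Primary outcome measures names safety as the second of two primary outcomes. The safety entry in Table 4 (Feasibility targets) reads: "Nil severe and/or serious adverse events rated as likely due to study intervention in the active FMT group".

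**The concern.** The rule joins two decisions that are better kept apart: stopping treatment and leaving the study. Because the adverse-event route is an alternative to withdrawn consent, a researcher may use it for a participant who is content to stay. That participant's safety follow-up, already consented to, then continues only if they agree to be contacted.

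The fit with this design is poor because dosing is over in four days. After that no dose remains to withhold, yet most of the safety observation is still to come. Any loss would also be selective, since it falls on people who have just had an event. The safety target is a zero count in the active arm, so a later event that goes unseen can only make the target easier to meet. This matters where the triggering event did not itself fail the target, either because it was neither severe nor serious or because it was not rated likely related. The Discussion presents the six-month safety follow-up as a feature of the design, which is a further reason to protect it.

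**Working it through.** No figure in the article is disputed. The only related one is the tolerated attrition in Table 4: (15 − 10) / 15 = 33.3%, which agrees with the stated 33%.

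**Step 1: does the rule reach a consenting participant?** The sentence on withdrawal gives withdrawn consent and researcher discretion as alternatives. The discretionary route therefore does not need withdrawn consent, and what is withdrawn from is the study. The follow-on sentence then asks about safety contact. If scheduled contact simply continued, the question would not be needed.

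**Step 2: what exposure can withdrawal still limit?** Dosing takes 4 of 26 × 7 = 182 days, or 4 / 182 = 2.2%. During days 1 to 4, stopping the enemas for an adverse event is legitimate, but that needs only treatment discontinuation. After day 4 nothing remains to stop.

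**Step 3: how many safety assessments become opt-in?** The adverse-event row of Table 1 is marked at appointments 2 to 10, which is 9 assessments. Appointments 2 to 5 are dosing days (4). Appointments 6 to 10, at weeks 2, 4, 6, 8 and 26, follow dosing (5). The number still to come depends on when withdrawal happens:

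- after day 4: 5
- after week 2: 4
- after week 4: 3
- after week 6: 2
- after week 8: 1

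**Step 4: what else does withdrawal remove?** At weeks 2 to 8 Table 1 also schedules depression ratings and questionnaires, with blood, stool and physical examination at weeks 2 and 8. Withdrawal before week 8 would presumably spare these as well, although the article does not state what happens to them. Each could be skipped without ending the adverse-event assessment. At week 26 the adverse-event row is the only one marked.

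**Step 5: what could a lost participant mean for the safety statement?** This is an illustration, not an estimate. With zero events among n followed, the exact one-sided 95% upper bound on risk is 1 − 0.05^(1/n). For n = 10 (the whole active arm) it is 25.9%; for n = 9 it is 28.3%; for n = 8 it is 31.2%. These figures assume that loss is unrelated to risk. Loss triggered by an adverse event would not meet that assumption.

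**Step 6: what would continued contact cost?** At most the 5 contacts in Step 3. The Table 1 footnote allows "all or parts of each appointment to be conducted by telehealth if this is preferable to the participant or required for other reasons". Study setting plans "10 study appointments, six of which are in-person and four via telehealth". By inference the in-person visits are the four dosing days plus weeks 2 and 8, where blood and physical examination fall, and the telehealth visits are screening and weeks 4, 6 and 26. On that reading 3 of the 5 post-dosing contacts would be remote anyway.

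**The case against.** The strongest reply is that the same section already deals with most of this. Reasons are documented and withdrawn participants are asked about safety contact. Consent can be withdrawn at any time, so a person who refuses when asked might equally miss visits under a default. The real loss is confined to people who would have attended by default but decline when asked. That narrows the point and stands as mitigation. It does not remove it, because the change from default to opt-in comes from a staff decision and falls on those with an event.

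A second reply is that an unwell or acutely suicidal participant may reasonably be relieved of blood draws and questionnaires. That is right. A reader might infer that withdrawal after day 4 serves no purpose at all; Table 1 does not support that reading for the period before week 8. What it supports is that such relief does not require leaving the study.

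Third, withdrawal after week 8 is the least likely case, since only one contact remains and nothing is scheduled in between. A reader might note that this window is 18 of 26 weeks (69%) and take that as the size of the problem. It is a share of calendar time only. One of the five post-dosing assessments is at stake there.

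Fourth, harm needs a chain: a triggering event that does not fail the target, a decision to withdraw, refusal of contact, and a later related severe or serious event in the active arm that reaches the team by no other route. The independent data safety monitoring board, the blinding of staff, and the fact that withdrawal before week 8 counts against the retention target all weigh against a strong reading. However, the board and the medical referral routes respond to events once known; they do not keep a withdrawn participant under observation.

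Finally, the article is condensed, and a full protocol may separate the two decisions. The point here concerns the rule as published. If the full text already separates them, only the published wording needs aligning.

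**Conclusion.** The point holds as a weakness in a stated rule, minor to moderate in a 15-person pilot. The researcher may withdraw a consenting participant from the whole study after an adverse event, and up to five post-dosing adverse-event assessments then depend on fresh agreement. After day 4 this limits no exposure, and any welfare benefit can be had by omitting individual procedures.

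The documents do not support reading this as a rule that biases the safety result in any known amount. The article gives no rate of such withdrawals and none of declined contact, so the number of participants affected cannot be estimated. Nor should a reader infer that the triggering event is lost: it is recorded, and only later events can be missed.

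The conclusion rests on reading the adverse-event route as independent of consent, and on reading the request for further contact as replacing scheduled follow-up. Both follow from the plain wording.

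**What to change.** Replace the rule with one or two sentences. An adverse event may lead to stopping the remaining enemas, or to omitting individual procedures on welfare grounds. Scheduled adverse-event assessments to week 26 continue by default, by telehealth if needed, unless the participant withdraws consent for them. Report enema discontinuations separately from study withdrawals, by reason and arm.

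The cost is matching wording in the consent form and at most five further safety contacts per affected participant. Nothing else in the design has to change.

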### Management of adverse events

#### Managing risk

On enrolment, all participants will be required to provide details for their current or preferred general practitioner. In the case of a participant reporting suicidal ideation, plan, or intent, (a MADRS suicide item score of 5 or 6), the researcher will strongly encourage the participant to contact their general practitioner, and the researcher will also attempt to contact the general practitioner directly. In the case that a more serious concern for the immediate safety of the patient arises, such as severe suicidality with immediate risk, or an unreported recent suicide attempt, the researcher will contact a psychiatrist member of the team or take immediate action to ensure participant safety. This may involve—with the participant’s consent—contacting the treating general practitioner or other treating clinician, assisting the person in accessing relevant care, for instance by contacting ambulance or psychiatric emergency services.

#### Safety requirements

Study participants will be provided with contact details for the research team, and strongly encouraged to contact the research team at any point in the study to report adverse events or discuss concerns. In addition to this, there will be routine contact made every 2 weeks post-intervention until the 8-week primary endpoint, and an additional 26-week follow-up, to assess adverse events or side effects. In the circumstance of a severe or serious adverse event, participants will be encouraged to attend medical services.

If a severe or serious adverse event occurs, the re-identification protocol may need to occur, so that treating clinicians can know whether the participant received the FMT intervention or the placebo. Each participant will be issued a unique identifying number on enrolment which will be linked to the intervention that they were allocated. The unblinded research assistant will be contacted to reveal the treatment allocation of the participant, only if necessary for their medical care.

A data safety monitoring board (DSMB) will be implemented comprising of a clinician, a statistician, and a pharmacist. All members of the DSMB will be independent of the research to avoid conflicts of interest. The role of the DSMB will be to oversee the safety of the study. This will involve reviewing the study protocol, PICF and consent procedures, safety monitoring procedures, procedures relating to confidentiality and adverse events arising during the course of the study. In the event of a severe or serious adverse event, the DSMB will be promptly notified and will decide on whether to pause recruitment or halt the study.

## Ethical, regulatory, and dissemination aspects

### Consent and enrolment

Following primary expression of interest, via any of the above listed recruitment pathways, eligible participants will be directed to the study webpage for more details, where they will be able to register an expression of interest to be contacted by a member of the study team. Potentially eligible participants will be provided with a PICF. They will also be asked to nominate a time for a member of the research team to call them to discuss the study further and book in an initial study appointment. Participants will be given the option of signing the PICF with a member of the research team either in-person or via telehealth. Signed consent must be provided prior to study enrolment.

Consent will also be obtained from participant to send reminder texts prior to appointments.

Should participants have any conditions or commitments that preclude them from participating immediately, participants will be asked to nominate their preferred starting date within the trial period. Consent will be obtained to send participants reminders via email and phone.

Consent will be confirmed again at the initial screening appointment. Participants will be made aware that they can withdraw consent (primary or extended) at any point

### Plans for return of results of research to participants

At the conclusion of this study, a summary of results including aggregated results and their personal microbiome analysis report will be returned to participants via email or postal mail depending on their preference.

